**ABSTRACT**

**Rationale**: While varenicline on its own is the most effective medication for smoking cessation, long-term abstinence is still relatively poor. The addition of tDCS as an adjunct to pharmacotherapy is a novel approach but one that is grounded in a growing evidence-base.

**Research Question/Objective**: The primary objective of this research is to provide preliminary evidence of the effectiveness of tDCS as an adjunct treatment to pharmacotherapy for smoking cessation. Does the addition of active tDCS to the left DLPFC improve the effectiveness of varenicline in the treatment of tobacco dependence? Does it make individuals more resistant to relapse in the long-term?

**Study Design**: Double-blind, sham-controlled, randomized clinical trial

**Setting**: A free Nicotine Dependence Clinic in downtown Toronto, Canada

**Participants**: Fifty daily dependent adult smokers seeking treatment to quit smoking

**Intervention and Procedures**: Twelve weeks of varenicline treatment plus tDCS (active: 20 minutes at 2 mA OR sham: 30 seconds at 2 mA, 19.5 minutes at 0 mA), daily (M-F) for the first 2 weeks and then every 2 weeks for the next 10 weeks. 2 FMRI scans at baseline and 1 scan at end-of-treatment. Eye-tracking viewing tests will be conducted at baseline, week 4, week 8,end-of-treatment and at 6 months follow up. Follow-ups at 6-months. A monetary delayed discounting task will be performed at baseline, end of treatment and at 6 months follow up.

**Measurements**: Expired CO, self-reported smoking, and subjective craving and withdrawal at each study visit, weekly self-reported smoking status (7day PPA) from end of treatment to 6 months. For fMRI: BOLD activation, perfusion, structural T1 mapping, DTI and functional connectivity. For Eye-tracking: attentional bias to substance-related cues, attentional bias to negative emotional cues and attentional bias to high-arousal/high-risk cues.

**Potential Impact**: For every two smokers who quit, one life is saved from a tobacco-related mortality. Therefore, even a small improvement in smoking cessation treatment effectiveness and long-term abstinence would decrease the prevalence of tobacco-related death and disease and save the health care system billions of dollars.

**BACKGROUND and RATIONALE**

Despite important strides in the decreasing the prevalence of smoking in North America, one in five adults still smokes tobacco. Current first line medications (nicotine replacement therapy [NRT], bupropion, varenicline) are only effective for some. As such, there has been much interest in optimizing the efficacy of existing treatments. Based on preliminary evidence from a pilot study in our lab using transcranial direct current stimulation (tDCS) as an adjunct to standard nicotine patch treatment, we now hope to demonstrate both the safety and superior efficacy of adding a tDCS treatment regimen to standard varenicline treatment in a randomized sham-controlled double-blind study. The present proposal aims to pilot this protocol in 50 participants as proof-of-concept, and to explore the potential neurobiological and physiological correlates of any treatment effect using magnetic resonance imaging (MRI) and eye-tracking, respectively.

Varenicline is the most effective pharmacotherapy available for the treatment of tobacco dependence (Cahill et al, 2013). However, like all treatments for smoking cessation, successful long-term abstinence is hampered by high rates of relapse (CDC, 2008). Relapse is often reported to be due to succumbing to cravings usually elicited by environmental cues (Janes et al, 2010). This vulnerability to relapse is hypothesized to be due to long-lasting neuroadaptations resulting from chronic exposure to nicotine (Robinson and Berridge, 2001). Specifically, the dorsolateral prefrontal cortex (DLPFC) is thought to exert control over cravings and reward related to smoking (Goldstein and Volkow, 2011). Drug-induced neuroplasticity is a hallmark of addiction (Koob and Volkow, 2010). Smoking cessation may not involve the unlearning of the behavior so much as new learning that can serve to override the old, especially under circumstances of strong craving. Deficits in plasticity induced by nicotine withdrawal (Grundey et al, 2012) could be the mechanism which underlies the long-lasting vulnerability to relapse that plagues many ex-smokers as it impairs the ability of the brain to learn how to decouple pairings between environmental cues and craving (Fraser and Rosen, 2012).

Transcranial direct current stimulation (tDCS) is a form of non-invasive brain stimulation that involves brief (e.g., 20-min) application of weak electric current (e.g., 2 mA) to the scalp. It increases excitability of neurons at the anode with 20-30% of the current going through the brain from anode to cathode so that both cortical and subcortical structures are stimulated. The procedure is very safe, convenient, and fast-acting with well-established parameters and a credible placebo manipulation (‘sham’ tDCS: 30-s stimulation) (Poreisz et al, 2007). It has the ability to modulate plasticity in specific brain areas (Nitsche and Paulus, 2001) and has established effectiveness in human laboratory models of addictive motivation (Boggio et al, 2008; 2009) and has been shown to decrease craving for cigarettes when the anode is placed over the left dorsolateral prefrontal cortex (dlPFC) (Fregni et al, 2008). However, studies to date have only examined the effects of tDCS on laboratory measures of motivation and smoking behavior rather than smoking cessation and relapse prevention in treatment-seeking smokers. The proposed research will begin to address these fundamental gaps.

*Functional activation: cue reactivity:* One of the most prominent models of addiction is incentive sensitization (Robinson and Berridge, 2001), where the brain mesocorticolimbic reward system is sensitized, and drug cues acquire motivational salience and become conditioned reinforces themselves. In the case of smokers, smoking-related environmental stimuli can elicit smoking urges and cravings, which in turn is associated with compulsive smoking and relapse. Most neuroimaging studies examining neural reactivity to smoking-related (compared to neutral) cues have shown that smokers exhibit increased activation in regions involved in reward, craving, emotions, and memory, as well as regions associated with visuospatial attention (Due, 2002), suggesting increased attention to stimuli of heightened attentional salience. One study found that hyper-activation in some of these regions and decreased connectivity with cognitive control networks predicted “slips” in abstinence (Janes et al, 2010), and behavioural and non-nicotinic pharmacological smoking interventions can normalize these brain responses relative to non-smoking controls (Culbertson et al, 2011; Franklin et al, 2011; Westbrook et al, 2013). However, only a small number of studies have examined the effect of varenicline treatment on smoking cue reactivity. Although these studies suggest that varenicline modulates relevant networks, none of these studies used a full 12-week treatment protocol one study only required 3 days of abstinence prior to the second scan (Loughead et al, 2013), and another study required subjects to be non-abstinent even after 3 weeks of medication (Franklin et al, 2011). Our study will address this gap in the literature by conducting fMRI scans at baseline and after 12-weeks of varenicline treatment in both the active and sham treated tDCS groups. The sham tDCS group will allow us to examine the effects 12-weeks of varenicline treatment on cue reactivity in both quitters and non-quitters. Furthermore, we can compare the treatment effects of active versus sham tDCS within-subjects by comparing the pre- and post-treatment scans. Active tDCS should reduce cue-reactivity by increasing plasticity of the left DLPFC.

*Functional activation: reward anticipation:* Most neurological models of addiction stress the importance of the mesocorticolimbic pathways in processing the reinforcing effects of drugs (Koob & Volkow, 2009). Drugs of addiction such as nicotine alter the sensitivity of the brain regions involved in motivation and reward (Robinson & Berridge, 2001). Many studies have shown that addicted individuals show blunted activations in response to non-drug rewards in these brain regions (Balodis & Potenza, 2015; Sweitzer et al., 2015). As a result, addicted individuals with impaired reward processing pathways may contribute to drug-seeking behaviors. Specific brain areas that could be responsible for these changes include: the ventral striatum (Peters et al., 2011), the nucleus accumbens (NAc) (Buhler et al, 2010, Sweitzers et al., 2015) and the anterior cingulate cortex (ACC) (Fedota et al., 2015). Specifically, previous studies have shown that individuals with lower ventral striatal activity during the reward anticipation task were more likely to smoke/relapse (Sweitzer et al., 2015). Another area of interest for nicotine addiction is the medial prefrontal cortex (MPFC), which contributes to goal-directed behaviours in response to reward expectation (Goldstein & Volkow, 2002). Lastly, varenicline has been previously implicated in the reduction of reward signaling and decreasing alcohol intake in humans and rodents (Franklin et al., 2011; Hendrickson et al., 2010). In a recent study, varenicline downregulated gain magnitude processing in the anterior cingulate cortex (ACC), an area associated with attentional control (Fedota et al, 2015). Specifically, varenicline decreased the impact of reward magnitude on ACC activity whereas nicotine increased ACC processing when anticipating a reward (Fedota et al., 2015). Thus, we will be examining differences in the above brain regions at baseline and comparing them with end of treatment scans. The sham tDCS group will allow us to examine the effects 12-weeks of varenicline treatment on reward anticipation in both quitters and non-quitters. Meanwhile, the active tDCS group will allow us to examine the effects of tDCS on reward anticipation compared to non-active tDCS.

**Study Objectives**

The primary objective of this research is to provide preliminary evidence of the effectiveness of tDCS as an adjunct treatment to pharmacotherapy for smoking cessation. The secondary objective is to examine the neurobiological and physiological adaptations that may occur as a result of tDCS treatment. **Research Questions**:

1. Does the addition of active tDCS to the left DLPFC improve the effectiveness of varenicline in the treatment of tobacco dependence? Does it make individuals more resistant to relapse in the long-term?
2. How and what extent does varenicline and tDCS treatment effect brain activity and structures using fMRI?
3. What is the impact of varenicline and tDCS on attentional bias using a validated eye-tracking paradigm?
4. What is the impact of varenicline and tDCS on impulsivity as measured by a validated monetary delayed discounting task?

**Hypotheses**:

1. The combination of varenicline treatment plus tDCS to the left DLPFC will improve smoking cessation outcomes and relapse rates in treatment seeking smokers.
2. Active tDCS will reduce fMRI BOLD response to smoking cues compared to baseline within-subjects and compared to sham tDCS between subjects. Those who quit smoking in the last 4 weeks of treatment will show a “normalization” of brain reactivity to smoking cues and reward anticipation relative to those who were unable to remain abstinent over the short term due to tDCS extinguishing the salient properties of smoking-related cues and reward anticipation.
3. Compared to baseline, varenicline treatment will reduce within subject attentional bias, as measured by parameters of visual scanning behavior (VSB), to smoking and negative emotional cues.
4. Active tDCS will reduce attentional bias to smoking and negative emotional cues compared to sham tDCS. Those who quit smoking in the last 4 weeks of treatment will show “normalized” attentional bias patterns to smoking cues and reward anticipation relative to those who were unable to remain abstinent over the short term. Subjective measures of cravings will be correlated with within-subject changes in attentional bias to smoking cues and reward anticipation.
5. Individuals with larger changes in attentional bias to smoking-related cues and/or negative emotional cues, and lower measures of attentional bias to high-arousal/high-risk cues will have higher rates of abstinence (less relapse). Attentional bias will be measured by parameters of visual scanning behaviour and through the analysis of visual scanning patterns (sequences of fixations).
6. The probability of remaining abstinent over the long term will be inversely correlated with VSB measures of novelty seeking behavior.
7. Active tDCS will reduce impulsivity compared to sham tDCS as measured by higher delayed discounting scores.

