**METHODS**

**Design**

This will be a double-blind sham-controlled two-arm randomized clinical trial. Fifty participants will be randomized (1:1) to each arm. Arm 1 will be active tDCS plus varenicline (n=25) and Arm 2 will be sham tDCS plus varenicline (n=25). Treatment duration will be 12 weeks. Subjects will be required to attend an in person assessment visit. They will then be randomized to a condition. Neuroimaging scans (fMRI) and eye-tracking tests will be conducted in all participants at baseline. Participants will undergo two scans at baseline on different days within the same week: one in a satiated state and one in a non-satiated state. The same tasks will be performed at each scan. s. Following the baseline fMRI scans and eye-tracking tests, subjects will start taking the varenicline simultaneous with starting the tDCS regimen whereby they will come to the clinic every day (Monday to Friday) for the first 2 weeks to undergo the stimulation (active: 20 minutes at 2mA, sham: 30 seconds at 2mA and then nothing). Their target quit date will be at the end of this 2 week period. They will return to the clinic every two weeks for the next 10 weeks for a booster tDCS session and to complete questionnaires. Eye tracking tests will be conducted at the end of the fourth and eighth weeks. At the end of the 12-week treatment period they will undergo a third fMRI scan and eye-tracking tests. For the next 14 weeks they will be contacted weekly by e-mail or text message to report on their smoking status as measured by the 7 day point prevalence abstinence question. “Have you had a cigarette, even a puff, in the last 7 days?” At the 6-month time point subjects will be asked to return to the clinic for a brief visit to confirm smoking abstinence using expired CO and urinary cotinine and to complete questionnaires.

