**Data Analysis**

Continuous data (cravings, mood, cigarettes smoked/day, CO) will be assessed with 2 Gender x 2 (Laterality) x 10 (session) Analyses of Variance (ANOVA). Parallel ANOVAs will assess self-report measures during post-treatment follow-up. Categorical data (e.g., # abstinent participants/session) will be assessed with chi-square, and Kaplan-Meyer survival analysis for repeated measures. Planned comparisons will be performed for the critical experimental conditions (active tDCS) vs. sham.

The critical metric will be Effect Size (partial η2 generated by SPSS), rather than p level. This will reveal the degree of efficacy for the primary outcome variable, Consecutive Days Abstinent (small = .01, medium = .06, large = .14), and allow us to estimate N required to achieve statistical significance for this effect (80% power, α = .05, two-tailed). Pearson correlations will explore the possible relationship between effects of tDCS (session 10 scores, controlling for session 1) and trait factors (e.g., FTND, age, gender, depression).Analysis of MRI data

For the neuroimaging data, brain imaging measures will be compared between groups and across time points, using analysis of variance. MRI measures will also be related to subjective responses (i.e., baseline scores and changes in craving, mood, and withdrawal) using linear regression.

fMRI data will be analyzed by fitting a general linear model (GLM) to the data time-series at every voxel across the brain (and/or within ROIs) and assessing effects using F/t-tests and % signal change calculations. Quantitative T1 maps and DTI analysis will be analyzed at the whole brain level and using ROIs.

After back-sorting by treatment outcome (achieved/maintained abstinence), we expect baseline measures to predict relapse, and active tDCS treatment to result in more efficient functional activation, . than sham tDCS at the second MRI scan.

Analysis of Eye-Tracking Data

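### Hypothesis 2 offers the active arm's fall from baseline in BOLD response as one sign of a tDCS effect, but only the comparison with sham can isolate tDCS

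*Protocol*

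**What the plan says.** The second hypothesis (Protocol, Hypotheses) reads: "Active tDCS will reduce fMRI BOLD response to smoking cues compared to baseline within-subjects and compared to sham tDCS between subjects". It puts two comparisons under one claim about active tDCS: the active arm against its own baseline, and active against sham.

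Both arms receive varenicline, with 25 participants each. After the baseline scans, "subjects will start taking the varenicline simultaneous with starting the tDCS regimen" (Design).

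The cue-reactivity paragraph of Background and Rationale expects cessation treatment to affect the measured response. On varenicline it says: "Although these studies suggest that varenicline modulates relevant networks". On other treatments it says that "behavioural and non-nicotinic pharmacological smoking interventions can normalize these brain responses relative to non-smoking controls". It gives the sham arm the task of showing this: "The sham tDCS group will allow us to examine the effects 12-weeks of varenicline treatment on cue reactivity". It then adds that "we can compare the treatment effects of active versus sham tDCS within-subjects by comparing the pre- and post-treatment scans".

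For the analysis, "brain imaging measures will be compared between groups and across time points, using analysis of variance" (Data Analysis). The group-by-time term is not named, and nothing says whether one or both parts of hypothesis 2 must hold for it to count as supported.

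**The concern.** The active arm's change from baseline to week 12 contains any effect of tDCS, but also 12 weeks of varenicline, a quit attempt, the passage of time and repeat scanning. A test of that change asks whether anything moved in people given all of this. It does not ask whether tDCS added anything. Since the protocol itself expects varenicline to affect these networks, the active arm may change even if tDCS is inert.

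At stake is the secondary objective, which concerns adaptations that result from tDCS (Study Objectives). Suppose the active arm falls significantly from baseline but shows no significant advantage over sham. Under the present wording that split result could be presented as partial support for a tDCS effect, although the controlled comparison did not show one.

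**Working it through.** **1. The protocol's two readings of within-subject change.**

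- Eye-tracking: hypothesis 3 assigns the fall from baseline in attentional bias to varenicline. Hypothesis 4 tests tDCS against sham. The eye-tracking analysis section repeats the split: within-subject comparison over sessions for varenicline, between-group comparison for tDCS.
- BOLD: hypothesis 2 assigns the same kind of within-subject change to active tDCS.

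The design is the same for both outcomes, so the two readings cannot both be right. The eye-tracking reading fits the design.

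**2. Size of the problem if the within-arm test is read alone.** The protocol states no effect size, SD or power for BOLD, so there is no figure of its own to reproduce.

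Inputs:

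- n = 25 per arm (Design), and n = 15, the lower end of the imaging range in Sample Size and Power Calculation.
- Two-sided α = 0.05. The protocol states this level and sidedness for sizing a later trial; using it here is an assumption.
- True tDCS effect = 0, with the same mean fall *d* in both arms, in SDs of the change score. Both the size and the direction of *d* are assumptions: the Background gives neither for varenicline.

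Formula: the probability of a significant fall in the active arm is P(T > t₀.₉₇₅,ₙ₋₁), where T is non-central t with n − 1 degrees of freedom and non-centrality *d*√n. For n = 25 the critical value is 2.064 and the non-centrality is 5*d*, that is 1.0, 1.5, 2.5 and 4.0. For n = 15 the critical value is 2.145 and the non-centrality is 3.873*d*, that is 0.77, 1.16, 1.94 and 3.10.

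The other two quantities come from 100,000 simulated trials per scenario.

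| Common fall *d* | Active arm alone, n = 25 | Active arm alone, n = 15 | Active vs sham on change, two-sided | Both parts favourable, n = 25 |
|---|---|---|---|---|
| 0.2 | 16% | 11% | about 5% | 2.0% |
| 0.3 | 30% | 19% | about 5% | 2.4% |
| 0.5 | 67% | 44% | about 5% | 2.5% |
| 0.8 | 97% | 82% | about 5% | 2.5% |

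**3. Why requiring both parts is safe.** The joint event lies inside the event that the between-arm test rejects in favour of active tDCS. With an inert tDCS that has probability 0.05 / 2 = 2.5%, so the joint probability cannot exceed 2.5% whatever *d* is. The simulated values, 0.8% to 2.6% over *d* from 0 to 1.0, agree within simulation error.

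**4. How often a split result would occur.** At *d* = 0.5 and n = 25: 67.0% − 2.5% = 64.5%. About 65% of trials of an inert tDCS would show a significant active-arm fall without a significant advantage over sham.

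**The case against.** The strongest reply is that the hypothesis joins its two parts with *and*. Read as a joint requirement, it protects against false credit to tDCS, as step 3 shows. The controlled comparison is also planned: the Background announces active versus sham on pre- and post-treatment scans, and the imaging analysis expects active tDCS to give more efficient activation than sham. Naming the interaction term is detail that a statistical analysis plan may supply. Research question 2 asks what varenicline and tDCS together do to the brain, so the active arm's change is a legitimate descriptive quantity.

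Much of this stands, and it rules out several stronger readings that a reader might infer:

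- *That the trial will accept the within-arm fall as sufficient.* No section says so. The 16% to 97% figures apply only if the sham comparison is set aside.
- *That the within-arm test rejects whenever varenicline or quitting changes the brain.* Rejection depends on the size of the shift and on n: at 0.2 SD it is 16% with 25 per arm and 11% with 15.
- *That those percentages are an inflated type I error.* The null of no change is false in every row of the table. The error would lie in attributing the change to tDCS.
- *That the Background sentence on comparing active and sham within subjects is itself wrong.* It is ambiguous, and its natural reading is a comparison of arms on change, which is the right one.
- *That significance in one arm and not in the other will be taken as a difference between arms.* No section plans this.

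What the reply does not remove is that the protocol never says both parts must hold, and that the within-arm part is worded as an effect of tDCS. Under the joint reading that part still adds nothing specific to tDCS.

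**Conclusion.** The point holds in a limited form. The comparison of the active arm with its own baseline cannot isolate tDCS, because varenicline starts at the same time in both arms and is expected to act on the same networks. Hypothesis 2 is also out of line with hypotheses 3 and 4.

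The consequence depends on how the hypothesis is read. If both parts are required, false credit to tDCS is at most about 2.5%. If the within-arm fall is read alone, an inert tDCS would appear to work in 16% to 97% of trials at n = 25, or 11% to 82% at n = 15, for common falls of 0.2 to 0.8 SD. That range is an assumption. A common shift in the other direction would instead make the within-arm part hide a real effect.

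This is a minor matter. Imaging is a secondary objective in a proof-of-concept pilot, and the comparison that is needed is already within the planned analysis.

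**What to change.** Reword hypothesis 2 so that the tDCS effect is tested only by the active-versus-sham difference in change. For example: *the fall in BOLD response to smoking cues from baseline to end of treatment will be larger with active than with sham tDCS*. The test is the group-by-time term, or the end-of-treatment response compared between arms with adjustment for the baseline scan. Since the Neuroimaging section plans two baseline scans, abstinent and satiated, the wording should say which one serves as baseline.

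Report within-arm change as descriptive, in line with hypotheses 3 and 4. The Background sentence needs no correction beyond matching wording.

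The cost is wording only: the same scans, participants and analysis-of-variance framework. What is given up is a comparison that could be met without any effect of tDCS.
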